The current study responds to the need for effective suicide prevention training for primary care providers [11]. The primary research question asks whether experiential and reflective practice, via standardized patient simulation and feedback, improve suicide prevention skills over and above expert teaching alone. We test simulation as a component of the training because, while resource-intensive, it involves techniques that are core tenets of adult learning and is highly likely to be effective [20]. We incorporate specific feedback into the training as it has been shown to be a key component of learning new skills in the medical field [21]. Assurance of providers’ ability to identify and effectively respond to those who are suicidal is an ideal use of simulation-based training and assessment methods [22]. We include telehealth as a modality in the experimental condition with the knowledge that it will soon be a normative practice for primary care providers and to contribute to our understanding of interventions with suicidal patients.

This randomized control trial (RCT) examines the effectiveness of simulation and feedback, using standardized patient (SP) interactions, on the suicide risk assessment and management skills of primary care providers-in-training. There are two groups: 1) a control group that receives online teaching delivered via brief videos and, 2) an experimental group that receives the same brief videos followed by two SP practice experiences with feedback – one face-to-face and one telehealth. Both groups’ skills are tested via an in-person SP “test case” at 6-month follow up. All SP interactions are followed by immediate feedback given by the SP that is specifically linked to training concepts.

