### Design

The study is a randomized controlled trial with an experimental group and a control group allocated with a 1:1 randomization ratio. All trainees are randomized to control and experimental learning groups using Wei’s urn randomization [23] which provides overall balance at the end of accrual but also gives good, often near-perfect, balance within many strata [24, 25]. Randomization strata include medical learner groups (i.e., medical residents, pediatric residents, and nurse practitioners) and gender. After all baseline measures are completed, participants are randomized to experimental condition by the project statistician, who remains blinded to study condition.

Participants in both groups complete a 48-min, 6-module, online video-based training on suicide prevention (Commitment to Living for Primary Care; CTL-PC). Upon completion of the online teaching program, participants in the experimental group engage in two standardized patient practice interactions over the course of 4 to 6 months. One practice interaction takes place in-person and the other uses a telehealth model. The order is randomized. Then, approximately 6 to 8 months (depending on schedules, see below) after video-based learning, both control and experimental groups engage in an in-person “test case” standardized patient interaction.

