### Procedures

Following enrollment, participants receive an email with instruction to complete online baseline assessments and view the teaching videos within 14 days. All surveys are completed online using the same secure website that hosts the CTL-PC videos. After they have viewed the videos, participants in the experimental condition engage in two practice SP interactions over a period of about four months, with at least one month between interactions. Participants in the control condition do not have practice interactions. At approximately six months following completion of online teaching, both experimental and control participants complete the same face-to-face SP test case. There are two SP character scenarios for the experimental practice sessions and one test case SP scenario.

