As part of their practice experience, experimental participants engage in telehealth and face-to-face SP interactions; the order of presentation is randomized. The SP practice character scenario is also randomized (male/female) for the experimental group. All interactions are video-taped for observational coding of suicide prevention skills. In the telehealth modality, the participant and standardized patient are in different locations and interact using a secure webcam service. The face-to-face modality occurs in an office setting. The procedures for face-to-face and telehealth interactions are the same and no more than one hour in duration, including: orientation to the procedures and the SP scenario backstory, up to 30 min for the SP interaction, 8 min for SP feedback for the participant, and 5 to 10 min for debrief procedures. Upon arrival to the interaction, participants are introduced to the procedures and are given a brief written backstory about the SP scenario. Backstories provide context for the provider and include details about the patient’s name, age, the nature of the patient-provider relationship, some medical and social history and the reason for this visit (“trouble sleeping”). Telehealth participants also receive instructions about remote access. Participants are instructed to assess the patient’s risk for suicidality and provide appropriate interventions within a 30-min timeframe (a timer signals the appointment end). After the interaction, participants exit the room for 10 min during which time the SP prepares immediate feedback (positive and constructive) for the patient. SPs are highly trained to prepare and deliver tailored feedback using a 15-item “feedback matrix” template of criteria for identifying appropriate feedback items. Feedback includes specific competency items with explanations and rationale for the importance of the skill. The participant joins the SP for 8 min to receive feedback, discuss the interaction and ask questions. Afterwards, the participant returns to the facilitator for 5 to 10 min of debrief procedures. During this time, participants are provided the opportunity to speak with a psychologist for further debriefing if needed.

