##### Feedback matrix

Immediately following each interaction, SPs prepare feedback for the participant on 15 items and document the ratings on a Scantron-style form. SPs verbally provide participants with six feedback items – three positive and three constructive. Several items are prioritized as feedback items to provide to the participant. In the case of experimental participants’ second and final sessions, SPs have information on the feedback items that have been previously provided to the participant as guidance for novel feedback.

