The primary hypothesis of the study is that participants in the experimental condition will demonstrate significantly better skills compared to the control group, as measured by reliable, observed ratings of behaviors in the SP assessment at 6 months. We will use ANCOVA to assess SP training effects at follow up on all participants’ skills. Skills will be measured by reliable observational ratings of several suicide specific and general interviewing skills. In all instances, gender, training program group, race/ethnicity, and age will be included as covariates to aid in statistical power [35, 36].

##### Exploratory analysis for hypothesis 3

We will examine statistical equivalence between the two SP modalities (face-to-face; telehealth). Similar to Hypothesis 1 (above), Tryon’s inferential confidence intervals will be used to assess for equivalency among face-to-face and telehealth modalities [31, 32]. Following Treadwell and colleagues [33], a standardized small effect of .20 [34] will define the criterion for establishing a MID. As a form of sensitivity, a MID of .10 will also be examined. As a second form of sensitivity, multilevel modeling will be used to decompose the variance associated with these observed training outcomes into variance attributed to the person as well as variance attributed to time (first SP interaction, second SP interaction) and variance attributed to modality. Since the order is randomized, we might expect more variance attributed to time (improving over time). Within these models, the learner (person) defines level 2 with the observed ratings being the dependent level one variables. Both time and modality will be entered as time varying covariates.

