##### Power analyses

Optimal Design software [43] was used to assess statistical power. As previously stated, covariates will be included in all models to help improve power to detect a treatment effect [35, 36]. Power will be computed on a modest effect size estimate of .30. With a minimum final sample size of 108 participants and explaining 40% of the variance in the outcome, we have .51 power to detect an effect size of .30. However, power increases to .80 if 50% of the outcome variance is explained by covariates. If 60% of the outcome variance is explained via covariates, we have greater than .80 power to detect an effect size of .20. We believe that an effect size of .30 is attainable and we also expect that baseline values of the dependent variable of interest as well as other baseline variables are likely to account for 50% of the variance in the dependent variable. While we recognize that power will be more limited for the exploratory questions addressed (and will supplement all analyses with the use of effect sizes), we do feel that the knowledge gleaned will provide useful information with regard to dissemination of the simulation training — addressing whether implementation via telehealth is statistically equivalent to in-person implementation as well as providing preliminary knowledge about the amount and predictors of change over time.

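### The face-to-face versus telehealth contrast compares in-session performance, so it cannot support the stated conclusion on equivalence of implementation by telehealth

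*Protocol article*

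**What the plan says.** The Design section states: "One practice interaction takes place in-person and the other uses a telehealth model. The order is randomized". Procedures repeats that "experimental participants engage in telehealth and face-to-face SP interactions; the order of presentation is randomized", and schedules "two practice SP interactions over a period of about four months, with at least one month between interactions". Both trial arms then take the same in-person test case (Procedures; Standardized patient scenarios).

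Teaching follows each session. According to the Background, "All SP interactions are followed by immediate feedback given by the SP that is specifically linked to training concepts". Procedures gives the sequence: an interaction of up to 30 minutes, then a break, then 8 minutes of feedback. At later sessions, "SPs have information on the feedback items that have been previously provided to the participant as guidance for novel feedback" (Feedback matrix).

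Under the exploratory analysis for hypothesis 3, Tryon's "inferential confidence intervals will be used to assess for equivalency among face-to-face and telehealth modalities", with a minimum important difference of .20 SD and .10 SD as a sensitivity margin. A multilevel model is a second sensitivity analysis: "Both time and modality will be entered as time varying covariates". The section on power then describes the result as "addressing whether implementation via telehealth is statistically equivalent to in-person implementation", as part of what the trial offers for dissemination of the simulation training.

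**The concern.** A programme deciding whether to deliver simulation training by telehealth needs to know whether trainees end up equally skilled. Two features of the design stand between the planned contrast and that question.

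- The only outcome measured after training is complete is the test case, and by then every experimental participant has had both modalities.
- The practice-session ratings, which do separate the modalities, are taken before the feedback of the session being rated. What session 1 teaches can appear only in session 2, which is always in the other modality.

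A finding of equivalence could then be read as evidence that telehealth training works as well as in-person training, when the data concern something else. A larger sample would not cure this.

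**Working it through.** **What each rating can reflect**

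| Rating | Modality | SP feedback received beforehand |
|---|---|---|
| Session 1 | the modality randomised first | none |
| Session 2 | the other modality | one session, in the first modality |
| Test case | in-person for all | two sessions, one in each modality |

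No row compares people taught by telehealth only with people taught in person only.

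**What the contrast estimates.** Let μ be mean face-to-face performance in session 1, d the telehealth minus face-to-face difference in performance, π a common period effect, and LF and LT what a first session teaches when it is face-to-face or telehealth.

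- Face-to-face first: session 1 = μ; session 2 = μ + d + π + LF. Telehealth minus face-to-face = d + π + LF.
- Telehealth first: session 1 = μ + d; session 2 = μ + π + LT. Telehealth minus face-to-face = d − π − LT.
- Average over balanced orders: **d + (LF − LT)/2**.

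The period effect cancels, and so does learning when LF = LT. Only unequal teaching remains.

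**Size.** The article gives no figure for LF − LT, so every value here is an assumption.

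| Assumed LF − LT (SD) | Shift in contrast (SD) | Against the .20 margin | Against the .10 margin |
|---|---|---|---|
| 0 | 0 | none | none |
| .20 | .20/2 = .10 | half | all |
| .40 | .40/2 = .20 | all | twice |

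The .40 row is an outer case: it exceeds the .30 that the article expects for the whole programme.

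**Does an order term change the modality estimate?** No. Order varies between people, while the modality contrast is within people. In a simulated sample of 20,000 with LF = .6, LT = .2 and d = 0, the face-to-face minus telehealth estimate was −.179 without an order term and −.179 with it (theory: −.20).

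**What order can show.** The two-session sums have means 2μ + d + π + LF (face-to-face first) and 2μ + d + π + LT (telehealth first). Their difference is LF − LT. A main effect of order in a model of single ratings is half of that.

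**Precision.** The article states no power for the modality comparison, so there is no figure to reproduce. With 108 participants allocated 1:1, about 108/2 = 54 are experimental and about 54/2 = 27 follow each order. Take SD 1 and an assumed within-person correlation ρ = .5:

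- Pooled modality contrast: SE = √(2(1 − ρ)/54) = √(1/54) = .136.
- Session 1 only: SE = √(2/27) = .272; 95% half-width about .55.
- Order contrast (sums): SE = √(2 × 2(1 + ρ)/27) = √(6/27) = .471; .44 to .50 for ρ from .3 to .7, with 95% half-widths of .88 to 1.01. Power to detect an LF − LT of .40 is 12 to 15%.

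**The case against.** The other side has a good deal on its side.

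- **Exploratory and hedged.** The analysis is labelled exploratory and the article admits limited power. This holds for severity. But the admission concerns precision, not which question is answered.
- **No evidence of unequal teaching.** Procedures says both modalities follow the same procedures; durations and the feedback template are shared, and the scenarios were matched for difficulty. A reader might infer that the contrast is biased in favour of telehealth. The documents do not support that: a shift arises only if teaching differs, and its direction and size are unknown.
- **Learning between sessions is not itself a bias.** Order is randomised and the sensitivity model includes time, so common learning cancels. This stands in full.
- **The order term.** A reader might infer that the model's lack of an order term is what prevents a valid equivalence conclusion. It is not, because adding the term leaves the modality estimate unchanged. Nor is its absence established: the sentence lists time-varying covariates, order is fixed for each person, and a condensed article may leave full specification elsewhere.
- **Loose wording.** Implementation may simply mean holding the encounter by telehealth. Elsewhere the article speaks of differences between modalities, which in-session ratings do address. That reading is possible, but the sentence ties the result to disseminating the training, and readers will take it so.

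**Conclusion.** The point holds as a mismatch between conclusion and design. The planned contrast estimates in-session performance by modality and, at any sample size, cannot show whether training implemented by telehealth is equivalent to training in person. This part needs no numerical assumption; it follows from everyone receiving both modalities and from each rated interaction preceding its own feedback.

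The possible shift is conditional: half of any difference in teaching, toward the modality that teaches less. The .10 SD example rests on an assumed difference of .20 SD; with equal teaching there is no shift.

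The consequence is minor to moderate. The analysis is exploratory, and the primary comparison of experimental and control participants at the test case is unaffected.

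**What to change.** 1. Restate the exploratory objective and the sentence under Power analyses, for example: *we will explore whether observed skills during a practice interaction are similar face-to-face and by telehealth; the design does not compare the effectiveness of training delivered by each modality.* Drop the conclusion on equivalence of implementation, and carry the same limit into the results paper.
2. As a supplement, tabulate ratings by randomised order and period. Report, with intervals, the order contrast (the difference in two-session sums estimates LF − LT; a model main effect estimates half of it) and the session-1 modality difference, which precedes any SP practice.
3. Say that these are descriptive and imprecise (SE about .47 SD for the sums and .27 SD for session 1, with 27 per order and an assumed correlation of .5), and that the order term does not correct the modality estimate.

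The cost is wording and two extra estimates from data already planned, with no change to design or sample size. The downside is a less favourable dissemination claim and wide intervals that settle little about which modality teaches more.

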##### Missing data

While we will make every effort to collect all data at each data collection point, missing data is likely. For analyses examining mean differences, pairwise deletion of missing data will be used, thus retaining all available information. As a form of sensitivity analyses, however, multiple imputation of missing data will be conducted. In short, multiple imputation uses a regression based approach to impute values for data that are missing. So that variance is not artificially constrained, multiple imputation incorporates random error into the imputation process [44, 45]. To improve estimates, the procedures put forth by Allison [46] regarding intervention studies will be followed. Here, each intervention condition is imputed separately and then the resulting datasets are merged. Following Rubin, [47] 10 imputations will be performed and each of the 10 resulting datasets will be analyzed as above. The results obtained from the 10 datasets will be combined following Rubin [47]. Multiple imputation has consistently demonstrated less biased estimates than most other traditional approaches to the handling of missing data (i.e., listwise, pairwise, mean imputation, single regression imputation) [44, 45, 48].

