#### Hypotheses and exploratory analyses

##### Hypothesis 1

All participants will demonstrate improved suicide prevention knowledge from baseline after viewing the online teaching videos. We anticipate that this improvement will be maintained at the 6-month SP assessment. We do not anticipate a difference between the two conditions on knowledge measures. Repeated measures analysis of variance will be used to examine change in knowledge scores. Time will be examined as a within-subject factor (pre, post-videos, and follow up) with group entered as a between-subjects factor. Specifically, we hypothesize an overall time effect but no group or group by time interaction effects. Tryon’s inferential confidence intervals (ICI) will be used to assess for equivalency across treatment groups immediately post videos and immediately after the SP test case [31, 32]. In general, these inferential confidence intervals are adjusted so that “statistical difference” equates to two inferential confidence intervals that do not overlap (i.e., abutting at the upper or lower bounds). Establishing traditional 95% confidence intervals about each of two means, and concluding that the means differ *p* < .05 if the two intervals do not overlap, constitutes a greater burden of proof of statistical difference than would a corresponding t-test. To establish equivalence, however, a “Minimum Important Difference” (MID) must be established a-priori. By establishing MID’s, a context for determining statistical difference, equivalence, and indeterminacy is provided. Statistical differences exist when ICI’s do not overlap; statistical equivalence exists when the maximum probable mean difference estimate provided by the ICI (maximum upper bound of mean 1 and 2 minus the minimum lower bound of mean 1 and 2) is less than the MID and statistical difference does not exist. Indeterminacy exists when the means are neither statistically difference nor significantly equivalent. Following Treadwell and colleagues [33] a standardized small effect of .20 [34] will define the criterion for establishing a MID. As a form of sensitivity, a MID of .10 will also be examined.

##### Hypothesis 2

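### Pairwise deletion does not keep all the data in the Hypothesis 1 repeated-measures ANOVA, which in its standard form drops anyone missing the post-video or follow-up knowledge score

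*Protocol article*

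**What the plan says.** The Missing data section expects some data to be missing and sets the main rule for comparisons of means: "pairwise deletion of missing data will be used, thus retaining all available information". Imputation comes second: "As a form of sensitivity analyses, however, multiple imputation of missing data will be conducted". It is specified in detail, with ten imputations, each arm imputed separately, and results combined by Rubin's rules. The section closes with a ranking of methods: "Multiple imputation has consistently demonstrated less biased estimates than most other traditional approaches to the handling of missing data", and the approaches listed are "i.e., listwise, pairwise, mean imputation, single regression imputation".

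Under Hypothesis 1, "Repeated measures analysis of variance will be used to examine change in knowledge scores". The layout is explicit: "Time will be examined as a within-subject factor (pre, post-videos, and follow up) with group entered as a between-subjects factor". Tryon's inferential confidence intervals are then used to assess equivalence of the two groups after the videos and again after the test case.

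The Design section fixes the order of events at entry: "After all baseline measures are completed, participants are randomized to experimental condition".

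**The concern.** Two stated choices do not fit together. The only reason given for putting pairwise deletion first is that it discards nothing. In a three-level within-subject ANOVA there is no pairwise option in the usual sense: a participant with a gap at one assessment contributes no complete vector and is removed, and the scores that were observed go too. For this model pairwise deletion becomes listwise deletion, and the reason for preferring it disappears. What remains is a method that the section itself ranks below imputation for bias.

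At stake is the estimate of knowledge gain and its maintenance. It would come from participants who completed every survey, with less precision than the data allow. It could also be biased if completing the surveys is related to knowledge. In addition, the two parts of Hypothesis 1 would rest on different sets of people: the ANOVA on those with all three scores, the equivalence intervals on everyone with a score at the given time.

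**Working it through.** The protocol states no figure that can be reproduced here. The check compares the stated rule with the stated model and then sizes the loss under assumptions.

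**Inputs**
- Sample size: 108, which is both the planned enrolment (Participants) and the sample used under Power analyses.
- Assessments in the model: three (Hypothesis 1).
- Assessments at which loss can arise: two, post-video and follow-up, because baseline precedes randomization (Design).
- Loss rate m at each later assessment: not given. Assumed range 5% to 20%.

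**Participants left in the ANOVA**

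If loss at the two later assessments is independent, the number with all three scores is 108 × (1 − m)². If the same people miss both, it is 108 × (1 − m), which is also the number with an observed follow-up score under either pattern.

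| m | independent: 108 × (1 − m)² | same people: 108 × (1 − m) |
|---|---|---|
| 5% | 108 × 0.9025 = 97.5 | 102.6 |
| 10% | 108 × 0.81 = 87.5 | 97.2 |
| 15% | 108 × 0.7225 = 78.0 | 91.8 |
| 20% | 108 × 0.64 = 69.1 | 86.4 |

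The difference between the columns is the number of participants who have a follow-up score but are dropped because the post-video score is missing. Under independence this is about 5, 10, 14 and 17 people. The baseline score of every dropped participant is lost as well, as is the post-video score of those missing only follow-up. If the same people miss both assessments, only baseline scores are lost. A mixed model would use all of these scores.

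**Can deletion bias the estimate?**

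A large simulated sample shows that it can. All settings are assumed: correlation 0.6 between assessments, true change 0.90 SD, and about 17% of follow-up scores missing, more often among those with low baseline scores.

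| Method | Estimated change (SD) |
|---|---|
| Truth | 0.90 |
| Complete cases | 0.84 |
| Difference of available means | 0.99 |
| Missing follow-up predicted from the two earlier scores | 0.90 |

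The two deletion methods err in opposite directions under one and the same mechanism. Participants with an observed follow-up have a baseline mean about 0.15 SD above the full sample. The complete-case change is then short by (1 − 0.6) × 0.15 = 0.06, and the difference of available means is too large by 0.6 × 0.15 = 0.09. The sign therefore depends on both the method and the mechanism. A likelihood-based mixed model rests on the same missing-at-random assumption as the prediction in the last row. It was not run separately.

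**The case against.** Much can be said for the plan. Multiple imputation is pre-specified, and each imputed dataset is to be analysed in the same way as the main data, so a Hypothesis 1 result using everyone will exist. The primary hypothesis is Hypothesis 3, a single-time-point ANCOVA. There, available-case analysis uses every observed test-case rating and loses little against imputation if missingness depends on arm and the model covariates. The equivalence intervals in Hypothesis 1 also compare group means at one time, where using all available scores is a fair description. All of this stands, and it confines the problem to the repeated-measures ANOVA. It does not remove it: the main Hypothesis 1 analysis still drops observed scores while the plan says that nothing is lost. The protocol does not itself say that incomplete participants are dropped. That follows from the standard form of the model it names.

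A reader might infer several stronger points that the protocol does not support:
- **Loss at all three assessments.** Cubing (1 − m) would give about 93, 79 and 66 of 108 at 5%, 10% and 15%. Baseline is complete before randomization, so these figures are too low.
- **Many participants lost from the ANCOVAs through missing covariates.** Training program and gender are randomization strata, and the other listed covariates are baseline data. Little loss is to be expected.
- **Completers exaggerate maintained gains.** In the simulation, complete cases understated the gain. No direction can be asserted.
- **Differential loss between arms.** The Discussion reports that sessions for residents in the experimental arm were hard to schedule and strayed from the timeline. That is delay. Missing surveys are possible but not reported.
- **Imputation must become the main analysis throughout.** For the single-time-point ANCOVAs this is a trade-off with little to gain.

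**Conclusion.** The point holds for Hypothesis 1. The Missing data section makes a claim that the three-wave repeated-measures ANOVA cannot meet in its standard form, and the same section ranks the chosen method below the one kept for sensitivity analysis.

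Under assumed loss of 5% to 20% at each of the two later assessments, between 97 and 69 of 108 participants would remain if losses are independent, and between 103 and 86 if the same people miss both. These are illustrations, since the protocol states no rate. Bias is possible, but its direction cannot be told from the document. The available-case ANCOVA for the primary skills outcome is not shown to be at fault.

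**What to change.** For Hypothesis 1, replace the repeated-measures ANOVA with a likelihood-based linear mixed model: time (three levels), group, and time by group, with an unstructured covariance across the three assessments, fitted to every observed score. With baseline complete, all randomized participants contribute. The model is valid if missingness depends only on observed scores and model terms, which the plan should state.

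In the Missing data section, limit the statement about retaining information to analyses for which it is true, such as the comparison of two group means at one time.

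For the single-time-point ANCOVAs, keep multiple imputation as the sensitivity analysis, and add baseline and post-video knowledge and self-efficacy to the imputation model as auxiliary variables. The primary skills ANCOVA does not list these among its covariates under Hypothesis 3, so this is where imputation could add information.

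The cost is a few sentences of analysis wording. No new data are needed, and multilevel software is already planned for the growth curve analyses.
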